**Primary outcomes**			
	Number of referred participants per individuals with LC^a^ (survivors of LC)	Questionnaire: cohort 1	
	Mean risk of LC in the referred population	Questionnaire: cohort 2 PLCOm2012 model	

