### Statistical Analysis

#### Quantitative Analysis

Participants with LC who refer at least one peer for participation will be compared to those who did not refer a peer for participation. To identify the predictive factors of referral, multivariable logistic regression will be used, adjusting for age, sex, educational attainment, health literacy, PAM score, and phase of LC trajectory. The dependent variable in the logistic regression will be referral by patients with LC. Using logistic regression, we will also examine if increased patient with LC activation is associated with increased odds of referral. Chi-square tests and 2-tailed *t* tests will be used for comparisons of categorical and continuous variables.

Referred participants who are eligible for LC screening will be considered as cases. A control group will be selected from patients who were either self-referred or referred by their primary care physician to the Quebec LC screening program and matched by age (1:1). To determine if participants in cohort 2 have a higher risk of LC than the controls, the mean PLCOm2012 scores will be compared using 2-tailed *t* tests in our cohort and in the Quebec LC screening program. The predictive factors of being eligible for LC screening and whether being referred by survivors of LC is associated with increased odds of being eligible will be examined using multivariable logistic regression. We will account for clustering among individuals referred by the same family member using a random effect model.

Spearman coefficients will be calculated to assess the correlations between the actual risk and the perceived risk of LC. Kruskal-Wallis tests will be used to compare actual and perceived risks of LC with different levels of anxiety. Odds ratios and their 95% CIs will be reported. All statistical analyses will be conducted using R (version 4.2.0; R Foundation for Statistical Computing).

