## Results

Enrollment in the cohorts was conducted from June 2023 to January 2024, with participants being followed up through July 2025. Overall, we have enrolled 25 survivors of LC who have referred 84 of their close contacts to this study. The results of this study are expected to be reported at the end of 2025 through publications in peer-reviewed journals and presentations at relevant national and international conferences.

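### The t test named for comparing mean PLCOm2012 carries neither the clustering by referring survivor, which the plan says it will account for, nor the 1:1 age matching

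*Protocol article*

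**What the plan says.** Table 1 of the protocol article lists as its second primary outcome "Mean risk of LC in the referred population", measured with PLCOm2012.

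The analysis is in Statistical Analysis, Quantitative Analysis, second paragraph:

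- Case group: "Referred participants who are eligible for LC screening will be considered as cases".
- Controls: people who referred themselves or were "referred by their primary care physician to the Quebec LC screening program and matched by age (1:1").
- Purpose of the comparison: "To determine if participants in cohort 2 have a higher risk of LC than the controls, the mean PLCOm2012 scores will be compared".
- Test, in the same sentence: "the mean PLCOm2012 scores will be compared using 2-tailed *t* tests in our cohort and in the Quebec LC screening program".
- Next, a model for eligibility: "whether being referred by survivors of LC is associated with increased odds of being eligible will be examined using multivariable logistic regression".
- Last sentence of the paragraph: "We will account for clustering among individuals referred by the same family member using a random effect model".

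The Results section gives the achieved numbers: "Overall, we have enrolled 25 survivors of LC who have referred 84 of their close contacts to this study".

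**The concern.** Contacts of one survivor are unlikely to have independent PLCOm2012 scores. The Introduction itself points to genetic factors and common exposures, including smoking, among relatives of patients with LC, and Limitations expects first-degree relatives to be over-represented. Smoking history feeds the score directly. Positive correlation within survivor is thus the protocol's own premise, and the last sentence of the paragraph acknowledges it.

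The test named for the mean comparison has no place for that correlation. If the random effect belongs only to the eligibility model just before it, the mean comparison is left unadjusted. If it is meant to cover everything in the paragraph, two incompatible methods are named for one comparison. The wording needs changing on either reading.

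Two further features do not fit. The controls are matched one to one on age, but nothing says that the t test is paired. And the cluster is defined by referral from a shared family member, whereas cohort 2 is anyone a survivor refers. Two friends of the same survivor form a cluster in the same sense but fall outside that definition.

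At stake is whether the p value for the comparison that addresses objective 2 means what it says.

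**Working it through.** **The plan's own figure.** The only sample size calculation concerns proportions, not mean PLCOm2012. Taking the 20% difference as 40% against 60%, two-sided alpha .05, power 80%, no continuity correction:

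n per group = [1.96 × √(2 × 0.5 × 0.5) + 0.8416 × √(0.4 × 0.6 + 0.6 × 0.4)]² / 0.20² = (1.3859 + 0.5831)² / 0.04 = 96.9, so 97.

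Two groups give 194, the stated figure. It contains no design effect, and nothing in it settles how the mean comparison handles clustering.

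**Inputs.**

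- From Results: 84 contacts and 25 survivors, so m = 84/25 = 3.36.
- From Quantitative Analysis: controls 1:1, each treated here as unclustered.
- Assumed, because the article gives no value: ICC 0.05 to 0.30; correlation within age-matched pairs ρ = 0 or 0.2; in one variant a cluster-size coefficient of variation (CV) of 0.8; in another, about half of the contacts eligible.

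**Formulas.** Design effect in the referred group: DE = 1 + (m − 1) × ICC. For an unpaired t test, the ratio of true to assumed variance of the difference is V = (DE + 1 − 2ρ)/2. True alpha = 2 × [1 − Φ(1.96/√V)].

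Example, ICC 0.10, ρ = 0: DE = 1 + 2.36 × 0.10 = 1.236; V = 2.236/2 = 1.118; √V = 1.057; 1.96/1.057 = 1.854; alpha = 6.4%.

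Example, ICC 0.10, ρ = 0.2: V = (2.236 − 0.4)/2 = 0.918; alpha = 4.1%.

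| | ICC 0.05 | 0.10 | 0.20 | 0.30 |
|---|---|---|---|---|
| DE, equal clusters | 1.12 | 1.24 | 1.47 | 1.71 |
| True SE / t-test SE (√V), ρ = 0 | 1.03 | 1.06 | 1.11 | 1.16 |
| Alpha, all 84, ρ = 0 | 5.7% | 6.4% | 7.8% | 9.2% |
| Alpha, all 84, ρ = 0, simulated | 5.3% | 6.8% | 7.5% | 9.2% |
| Alpha, uneven clusters (CV 0.8), ρ = 0 | 6.3% | 7.7% | 10.4% | 13.0% |
| Alpha, about half eligible, ρ = 0, simulated | 5.5% | 5.2% | 6.4% | 7.1% |
| Alpha, all 84, equal clusters, ρ = 0.2 | 3.5% | 4.1% | 5.4% | 6.8% |

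The uneven row replaces m by m × (1 + 0.8²) = 5.51. The simulations used 25 clusters (9 of size 4 and 16 of size 3, total 84) and 5,000 replicates, so each rate has a Monte Carlo error of about √(0.05 × 0.95/5000) = 0.3 percentage points. That explains why the half-eligible row is not monotone.

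**If the t test were paired.** Pairing would carry the matching but still not the clustering. The variance ratio becomes (DE + 1 − 2ρ)/(2 − 2ρ). With ρ = 0.2 this is (DE + 0.6)/1.6 = 1.07, 1.15, 1.30 and 1.44, giving alpha of 5.9%, 6.7%, 8.5% and 10.3%. The offset from matching exists only while the matching is ignored.

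**The mean itself.** An interval around the mean risk of the referred group that treated all 84 as independent would be too narrow by √DE: 1.06, 1.11, 1.21 and 1.31 across the same ICC values with equal clusters.

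**The case against.** A reader might infer that the plan ignores clustering altogether. It does not: the commitment stands in the same paragraph as the t test and is not expressly confined to the logistic model. This is also a condensed article, and a fuller plan may settle the scope. That removes any charge of oversight. It does not remove the mismatch, because the article goes beyond leaving a detail open: it names a specific test, and that test cannot hold a random effect.

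A reader might also conclude that the standard error is certainly too small and the false-positive rate certainly inflated. The document does not support that. It gives no ICC. The paragraph defines cases as eligible contacts but then speaks of cohort 2, so fewer than 84 may be analysed and the clusters may be smaller. Unmodelled age matching works in the opposite direction and could make an unpaired test conservative. These objections stand, and they limit the size of the point. They do not make the t test sound, since one unmodelled feature should not be relied on to cancel another.

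It is tempting to add that the confidence interval for the primary outcome is too narrow. The article specifies no interval for the mean risk; it promises intervals only for odds ratios. The √DE factors apply only if a naive interval is later reported. Likewise, the Spearman coefficients come with no stated test, so no fault is shown there.

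**Conclusion.** The point holds as a mismatch between the named test and the data structure that the same paragraph describes. As written, the mean PLCOm2012 comparison would use a standard error that reflects neither the referral clusters nor the matched design, and the definition of the cluster is too narrow.

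The likely consequence is modest. Across the assumed ranges with equal clusters and an unpaired test, the true alpha lies between about 3.5% and 9.2%. Only markedly uneven cluster sizes, or a paired test without clustering, take it above 10%, and then only at the upper end of the assumed ICC range. The net direction cannot be settled from the document. The mismatch and the cluster definition rest on no assumed number; every alpha figure does.

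**What to change.** In Quantitative Analysis:

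1. Replace the t test for mean PLCOm2012 by a linear mixed model with a random intercept for the referring survivor, or by a linear model with small-sample cluster-robust standard errors on that cluster. Keep the difference in means as the estimate.
2. Account for age in that model, through the matched pair or by adjustment.
3. Define the cluster as all contacts referred by the same survivor, whether relatives, friends or others.
4. State which analyses the clustering adjustment covers, and whether the comparison uses all of cohort 2 or eligible contacts only.
5. Use the same cluster-adjusted standard error for any interval reported around the mean risk of the referred population.

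A log transformation with geometric means is not needed; it would move the comparison away from the stated mean.

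The cost is a few sentences and a few lines of R, with no new data. Intervals may become somewhat wider.

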Survivors of LC are empowered with valuable knowledge on their disease’s trajectory, from diagnosis to treatment. By sharing their stories within their communities, they can empower other individuals in similar health states. Due to a combination of both genetic and shared risk factors such as smoking or exposure to radon, individuals with a first-degree relative with a history of LC have a 2- to 3-fold higher risk of LC compared to the general population [17]. In a qualitative study, among individuals eligible for LDCT screening per the US Preventative Services Task Force, Roth et al [18] demonstrated that having friends or family members being treated for LC was a major motivator for being screened themselves.

So far, no previous studies have examined the impact of using survivors of LC as sources of education and referral for peers and family members who may be eligible for screening. We hypothesize that survivors of LC would be willing to refer family members or peers to LC screening, leading to a positive impact on the uptake of both the preventative and screening behaviors of the referred population. This study thus aims to determine the feasibility and acceptability of referral to LC screening through patients with LC referring their close ones to LC screening and to assess the early impact of this novel recruitment strategy on the uptake of LC screening and the patients’ outcomes.

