### Objectives

We aim (1) to examine if patients with LC are willing to refer family members or close contacts to LC screening and if referral is associated with increased patient activation; (2) to examine if targeted enrollment of family members or close contacts of patients with LC for LC screening leads to increased engagement of individuals at higher risk of LC compared to referral through usual care; and (3) to examine the barriers and facilitators on the uptake of preventative strategies and LC screening, based on perceived genetic and clinical LC risks.

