**Figure 1 figure1:**
[figure not shown]
Screenshot of the web page for survivors of lung cancer and their close contacts. LC: lung cancer.

Patients interested can consent and enroll through this study’s website using digital or paper forms. Participants are invited to provide contact information (email or phone number) for the close ones they wish to refer for inclusion in the second cohort of our study. They are also advised to inform their close contacts that they shared their details with the research team and that their informed consent will be mandatory before participation.

#### Cohort 2

The second cohort includes participants being referred for inclusion into our study by the participants of cohort 1. Referred participants should be aged older than 18 years. Individuals with a personal history of LC are excluded. Referred participants are contacted by our research team through emails, phone calls, or through a recruitment pamphlet mailed for those without internet access. Participants are encouraged to access our study’s website [19]. The web page section directed at cohort 2 (Figure 1B) provides general information on LC, its epidemiology, information on LC screening programs and the risk-based eligibility, and information on risk mitigation strategies such as smoking cessation and home radon testing. The enrollment of referred participants is also carried out with a submittable digital form available on this study’s website. Participants lacking the digital literacy to enroll by themselves are contacted by the research team to enroll over the phone or through mailed material.

Once enrolled, participants have their 6-year risk of LC estimated with the PLCOm2012 (Prostate, Lung, Colorectal and Ovarian Cancer Screening Trial) risk model [20]. The risk prediction PLCOm2012 model has been extensively validated in previous studies [21,22]. The PLCOm2012 model has also shown adequate properties to discriminate patients with LC in a large cohort of Quebec smokers [23]. Moreover, data from the International Lung Screening Trial have shown that the PLCOm2012 model was more efficient compared to the US Preventative Services Task Force 2013 criteria to identify high-risk individuals to enroll into LC screening programs [24]. Participants who meet the eligibility criteria for the provincial LC screening program (ie, aged between 55 and 74 years and PLCOm2012 score ≥2%) are directed toward the provincial LC screening program to complete LDCT.

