### Sample Size

Preliminary data from the provincial LC screening program indicate that 40% of patients either referred to the program by their primary care physician or via self-referral meet the eligibility criteria for LC screening. The McGill University Health Centre receives approximately 800 new patients with LC annually, and the provincial LC screening program receives around 100 referrals each month. With a sample size of 194 referred participants, we will be able to detect a 20% difference in the rates of referral, with a power of 80% and an α value of .05.

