### Limitations

This study should be interpreted considering the following limitations. First, the recruitment is conducted in clinical settings based on patients receiving in-person care, either through approaching patients with LC directly or via self-referral to our study’s website after viewing study-related posters or pamphlets in the waiting areas of clinics. Patients who receive telemedicine follow-up care (such as teleconsultations with health providers and real-time counseling) are then less likely to enroll in this study. This recruitment strategy may introduce a selection bias with a selection of participants in better health states who can participate in this study, living closer to this study’s urban health care center, or with a larger social network that supports them in their travel to this study’s site. However, this bias appears limited as telehealth for LC care remains marginal at our institution, as also stated in a review of telehealth in LC during the COVID-19 pandemic [47].

Second, when potential participants are approached in person or view our study’s recruitment material in the clinics, those accompanying them are exposed to the same discussion and material. Therefore, the referred cohort may be biased to preferentially include the first-degree relatives of survivors of LC as these are the close contacts most likely to accompany patients to their clinical appointments. Friends or more distant relatives of survivors of LC may ultimately be underrepresented in the referred cohort.

To finish, this study is conducted among a cohort of residents in Quebec, where public health care expenses are covered for citizens. The generalizability of the results is limited to similar populations and health care systems, and caution is needed when generalizing results to other Canadian provinces or countries.

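### The clustering rule for the eligibility model names the same family member as the unit; it should name the referring survivor, so that friends referred by one survivor are clustered too.

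*Protocol article*

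**What the plan says.** The Quantitative Analysis section plans to examine "whether being referred by survivors of LC is associated with increased odds of being eligible will be examined using multivariable logistic regression". The comparison group is program patients who referred themselves or were referred by their physician. The section then gives its only clustering rule: "We will account for clustering among individuals referred by the same family member using a random effect model".

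Elsewhere the article describes a wider referred population:

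- The Background hypothesis is that "survivors of LC would be willing to refer family members or peers to LC screening".
- The first objective is "to examine if patients with LC are willing to refer family members or close contacts to LC screening".
- Under Participants Eligibility and Recruitment, "The second cohort includes participants being referred for inclusion into our study by the participants of cohort 1". No family tie is required.
- Data Collection (Cohort 1) puts extra questions to survivors who referred relatives only, so others are expected to refer people outside the family. It also records the survivor's relationship to each person referred.
- Limitations says "Friends or more distant relatives of survivors of LC may ultimately be underrepresented in the referred cohort", so friends may be few but are expected.

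**The concern.** The dependence arises because several contacts share one referring survivor. They may share smoking habits, social circle, neighbourhood and that survivor's choice of whom to name. This applies to friends as well as relatives. For a friend, though, the referrer is not a family member, so an analyst who follows the clause exactly would give each friend a separate cluster. No other sentence in the article widens the rule.

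At stake is the precision of the eligibility contrast. If positively correlated contacts are analysed as independent, the standard error is too small, the 95% CI too narrow and the false-positive rate above its nominal level. Because relationship is recorded, both codings can be produced from the same data and they give different intervals. The choice should be fixed before results are seen.

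**Working it through.** **Inputs from the article.** 25 survivors referred 84 contacts (Results), so the mean cluster size is 84/25 = 3.36. Controls are matched 1:1, taken here as 84. The eligible proportion in the program is 40% (Sample Size).

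**Assumed, because the article does not give them.** Latent ICC 0.1 to 0.3; friends 25% to 75% of contacts.

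**The plan's own figure.** For 40% against 60%, two-sided α .05, 80% power and pooled variance:

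n per group = [1.96 × √(2 × 0.5 × 0.5) + 0.842 × √(0.24 + 0.24)]² / 0.2² ≈ 97, and 2 × 97 = 194.

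The stated 194 is reproduced as the total of two groups. This reads the 20% as a difference in eligibility, although the article labels it as rates of referral. The figure contains no clustering term, so it does not settle what the cluster is.

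**Reference case: clustering ignored for every referred person.** With design effect DE = 1 + (3.36 − 1) × ICC in the referred group and independent controls, the true standard error is √((DE + 1)/2) times the naive one.

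| ICC | DE | SE ratio | Two-sided type I error |
|---|---|---|---|
| 0.1 | 1.236 | √1.118 = 1.06 | 6.4% |
| 0.2 | 1.472 | √1.236 = 1.11 | 7.8% |
| 0.3 | 1.708 | √1.354 = 1.16 | 9.2% |

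This is an approximation: it assumes equal cluster sizes and takes the ICC on the scale of the proportion. The literal rule should do less harm, because relatives stay clustered.

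**Simulation of the literal rule.** 84 contacts from 25 survivors, 84 singleton controls, 40% eligible in both groups, random-intercept logistic model. Results from separate runs of 500 and 600 replicates per setting:

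| Latent ICC | Friends | Family-member rule | Survivor as cluster |
|---|---|---|---|
| 0.1 | 25% | 4.2% | 4.0% |
| 0.1 | 50% | 4.2%; 7.0% | 3.4%; 6.2% |
| 0.2 | 25% | 7.5% | 7.0% |
| 0.2 | 75% | 7.4% | 5.6% |
| 0.3 | 25% | 6.4%; 6.8% | 4.4%; 5.7% |
| 0.3 | 75% | 8.4%; 8.3% | 5.6%; 5.5% |

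Two values in a cell come from two runs. A further run of 400 replicates over the same ranges gave about 5% to 9.5% against about 4% to 6%.

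The Monte Carlo standard error is about 1 to 1.5 points; for example, √(0.095 × 0.905/400) = 1.5 points. Single cells therefore move by a point or more between runs, and the upper 9.5% is not distinguishable from the 9.2% in the reference case. The gap within a row is steadier: 0.2 to 0.8 points at ICC 0.1, 0.5 to 2.0 points at ICC 0.2 or 0.3 with 25% or 75% friends except at the extreme, and 2.8 points (8.4 − 5.6 and 8.3 − 5.5) at ICC 0.3 with 75% friends.

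**Does the rule move the odds ratio?** In 500 replicates with 40% against 60%, about 60% relatives and a mean cluster size of 3.36, the median odds ratio with all contacts clustered by survivor against friends left as singletons was 2.40 against 2.44 at ICC 0.10, and 2.58 against 2.57 at ICC 0.20. The shift is at most about 0.04, so the effect is on the standard error.

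**The case against.** The best defence is that the phrase is loose wording for the referrer. The clause speaks of who did the referring, the only referrers are cohort 1 participants, and nothing asks for a survivor's contacts to be split into relatives and friends. The grouping variable might also be spelled out in a fuller plan. Friends are expected to be underrepresented, which points to the rows with little inflation, and this is a secondary contrast in a study that calls itself a pilot.

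Most of this stands as to size: the defect is small, and a sensible analyst may well cluster by survivor anyway. It does not remove the point. The article does not leave the unit open; it states one, and that unit is narrower than the cohort it describes. The same section uses exact terms for survivors and peers.

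A reader might infer three stronger things, none of which the documents support:

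- *That unclustered friends inflate the odds ratio.* They do not, as the simulation shows. A random-intercept odds ratio does lie further from 1 than the population-average 2.25 for 40% against 60% (2.28 to 2.82 at ICC 0.02 to 0.30), but that happens with correct clustering too; it is a different and legitimate estimand.
- *That the random effect is undefined for controls.* Controls share no survivor, so they are ordinary clusters of one. Nothing in the article codes them as a single cluster.
- *That a population-average scale or GEE is required.* The question is worded in terms of odds, and "Odds ratios and their 95% CIs will be reported" answers it. The proportion eligible is already a named secondary outcome, and the 20% is a planning assumption, not a promised reporting scale.

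**Conclusion.** The point holds as a defect in the stated cluster unit, with a small effect on precision. Read literally, the rule leaves friends of one survivor unclustered and makes the standard error of the eligibility contrast somewhat too small. Type I error is then about 5% to 9.5%, against about 4% to 6% with the survivor as cluster. Those ranges rest on the assumed ICC and share of friends and on the enrolled 84 contacts from 25 survivors. If the ICC is near 0.1 or friends are few, the difference is negligible. The conclusion does not extend to bias in the odds ratio, to the handling of controls or to the choice of a random-effect model.

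**What to change.** In the clustering sentence, replace *the same family member* with *the same referring survivor of LC (cohort 1 participant), for relatives and friends alike*, and add that each program control forms its own cluster. The random-effect model can stay.

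The cost is wording only. Contacts enter the study through the survivor who names them and the relationship is recorded, so no new data are needed. Confidence intervals become slightly wider: by less than about 6% to 16% at ICC 0.1 to 0.3 on the approximation above, since those figures compare with ignoring clustering altogether. Showing the percentage-point difference in eligibility beside the odds ratio would help readers but is optional.
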